## Abstract

**Introduction::**

Sepsis and septic shock are the most severe forms of infection affecting predominantly elderly people, preterm and term neonates, and young infants. Even in high-income countries sepsis causes about 8% of admissions to pediatric intensive care units (PICUs). Early diagnosis, rapid anti-infective treatment, and prompt hemodynamic stabilization are crucial for patient survival. In this context, it is essential to identify the causative pathogen as soon as possible to optimize antimicrobial treatment. To date, culture-based diagnostic procedures (e.g., blood cultures) represent the standard of care. However, they have 2 major problems: on the one hand, in the case of very small sample volumes (and thus usually in children), they are not sufficiently sensitive. On the other hand, with a time-to-result of 2 to 5 days, blood cultures need a relatively long time for the anti-infective therapy to be calculated. To overcome these problems, culture-independent molecular diagnostic procedures such as unbiased sequence analysis of circulating cell-free DNA (cfDNA) from plasma samples of septic patients by next-generation sequencing (NGS) have been tested successfully in adult septic patients. However, these results still need to be transferred to the pediatric setting.

**Methods::**

The Next GeneSiPS-Trial is a prospective, observational, non-interventional, multicenter study used to assess the diagnostic performance of an NGS-based approach for the identification of causative pathogens in (preterm and term) neonates (d1–d28, n = 50), infants (d29 to <1 yr, n = 50), and toddlers (1 yr to <5 yr, n = 50) with suspected or proven severe sepsis or septic shock (according to the pediatric sepsis definition) by the use of the quantitative sepsis indicating quantifier (SIQ) score in comparison to standard of care (culture-based) microbiological diagnostics. Potential changes in anti-infective treatment regimens based on these NGS results will be estimated retrospectively by a panel of 3 independent clinical specialists.

**Discussion::**

Neonates, infants, and young children are significantly affected by sepsis. Fast and more sensitive diagnostic approaches are urgently needed. This prospective, observational, non-interventional, multicenter study seeks to evaluate an NGS-based approach in critically ill children suffering from sepsis.

**Trial registration::**

DRKS-ID: DRKS00015705 (registered October 24, 2018). https://www.drks.de/drks_web/navigate.do?navigationId=trial.HTML&TRIAL_ID=DRKS00015705

## Introduction

1

Sepsis and septic shock are the most severe forms of infection.^[1]^ In addition to elderly patients, sepsis affects most often young children, as well as term and, in particular, preterm neonates, causing about 8% of admissions to pediatric intensive care units (PICUs) in high-income countries.^[2–8]^ Worldwide, an estimated 1.2 million cases of childhood sepsis occur each year.^[3,8]^ Therefore, with 2202 cases per 100,000 live births, the main burden is on neonates. Moreover, beyond the newborn period, children with chronic diseases have an increased risk of developing sepsis including hematologic and oncologic diseases, metabolic, neurologic, cardiac, and renal diseases as well as solid organ transplanted children.^[9]^ Both in adults and children, the triad of early diagnosis, rapid initiation of a causal therapy (consisting of a broad anti-infective therapy with prompt source control), and immediate hemodynamic stabilization is pivotal for patient survival. While the initial antimicrobial treatment regimen has to be empirical in most cases, the identification of the causative pathogen is crucial for patient disease course. This is due to the fact that an early de-escalation of the antibiotic regime, defined as the change from a broad-spectrum antibiotic agent to one with a narrower spectrum, is associated with lower mortality in patients with sepsis or septic shock.^[10]^ However, it is only safe to de-escalate within the first 72 hours once culture-results are available. But although these culture-based methods still represent the gold standard for pathogen identification today, they are associated with considerable limitations.^[11,12]^ First of all, culture-based methods are associated with a relevant time delay. Depending on the amount of microbes as well as the particular species in the original sample, it takes up to 5 to 7 days until the final results, including resistance patterns, are available.^[13]^ Secondly, they are often false-negatives. Even in highly selected patients suffering from proven endocarditis, using 1 set of blood cultures (1 aerobic and 1 anaerobic bottle, 8–10 mL each), bacteremia or fungemia can be detected with a sensitivity of around 70%.^[14]^ Sensitivity increases to 80% to 90% with the second set of blood cultures and over 98% can be achieved with the third.^[14]^ In less preselected patients with septic shock due to various infection foci, positive rates of blood cultures were only at 11%.^[15]^ In small children, positivity rates are even lower as such volumes (6 × 10 mL = 60 mL) cannot be collected in young children (e.g., a term newborn with a bodyweight of around 3 kg has a blood volume of only about 240 mL) without resulting in severe hemodynamic instability. As a result, blood-cultures of pediatric patients with sepsis remain negative in >90% of cases,^[16]^ making a reliable de-escalation of the antibiotic treatment regime more difficult. Thirdly, culture-based methods for pathogen detection have a high risk of contamination, whereby the results become false positive. As a result, patients suffering from sepsis or septic shock are frequently over-treated with antimicrobial drugs which, in turn, favors the selection of multi-drug resistant pathogens and increases the risks of drug-related toxicities. The latter are particularly significant in preterm and term neonates, in which detoxification-systems have not yet been fully developed.^[17]^

In order to overcome these challenges, we recently introduced the concept of an unbiased sequence analyses of circulating cell-free deoxyribonucleic acid (cfDNA) by next-generation sequencing (NGS) for sepsis diagnostics.^[18–20]^ Using a quantitative score (sepsis indicating quantifier [SIQ] score), this NGS-based approach enables clinicians on the one hand to identify the relevant infecting organisms and on the other to differentiate the sepsis-causing pathogen from potential microbial contaminants (e.g., coagulase-negative staphylococci). Therefore, this method has proven to be superior to state-of-the-art molecular approaches for the diagnosis of infecting organisms (such as polymerase chain reaction [PCR]-based methods for pathogen identification) in specimens of septic patients. In contrast to these conventional PCR-based diagnostic procedures, NGS is an open approach and therefore not limited to the identification of a predefined list of probable species.

As newborns, infants, and toddlers are particularly susceptible to the toxic side effects of anti-infective drugs due to immature detoxification systems, they could exceptionally benefit from this quicker, more sensitive diagnostic tool, needing only 1 mL of patient blood.

## Question and justification of the project (rationale)

2

This prospective, observational, non-interventional, multicenter study on the diagnostic use of NGS in neonates (d0–d28, n = 50), infants (d29 to <1 yr, n = 50), and toddlers (1 yr to <5 yrs, n = 50) suffering from severe sepsis or septic shock is designed to provide evidence for the effectiveness of an NGS-based approach in the quantitative measurement of pathogen load in blood samples from patients in the above-mentioned age groups. It is a clinical trial on a new technique designed to overcome a long-lasting problem on pediatric intensive care units and to replace the previous culture-based gold standard of microbial diagnosis in septic children. The study protocol of the Next GeneSiPS-Trial is very close to that of the Next GeneSiS-Trial, which investigated the performance of an NGS-based approach using the SIQ-Score in 500 adult patients with sepsis and septic shock.^[21,22]^ After a successful interim analysis of the Next GeneSiS-Trial, the Next GeneSiPS-Trial now seeks to extent the findings to newborns, infants, and toddlers.

## Objectives

3

First of all, the Next GeneSiPS-Trial aims to evaluate the performance of a NGS-based approach for the detection of the relevant infecting organisms in newborns, infants, and toddlers with suspected or proven severe sepsis or septic shock by the use of the quantitative sepsis indicating quantifier (SIQ) score in comparison to standard (culture-based) microbiological diagnostics. Second, we plan to assess the clinical value of NGS-based diagnostics asking a panel of 3 independent clinical experts to retrospectively identify potential changes in patient management strategies based on the presented NGS results.

Moreover, secondary objectives will be assessed:

Evaluation of antimicrobial resistance patterns and virulence factors.Evaluation of processing times for NGS-based measurements.Diagnostic or prognostic value of host nucleosome positioning patterns derived from plasmatic cell-free DNA in patients with suspected or proven severe sepsis or septic shock.^[23,24]^Diagnostic value of host expression profiles including RNA-derived biomarkers in patients with suspected or proven severe sepsis or septic shock.Examination of the metabolome in plasma and urine to identify risk profiles.

## Trial design

4

The Next GeneSiPS-Trial is a prospective, observational, non-interventional, multicenter study. This study protocol follows the Standard Protocol Items: Recommendations for Interventional Trials (SPIRIT) guidelines (see Supplemental File 1).

## Methods

5

### Study setting

5.1

The Next GeneSiPS-Trial will be carried out as a multicenter study on pediatric and neonatal intensive care units (PICUs and NICUs) of tertiary care hospitals throughout Germany. The Department of Anesthesiology and Intensive Care Medicine, Essen University Hospital, will coordinate the study in close cooperation with the clinical studies coordination center of Heidelberg University, Heidelberg (Germany). The Institute for Medical Biometry and Informatics (IMBI), Heidelberg (Germany) is responsible for data management and will provide statistical analysis. The Fraunhofer Institute for Interfacial Engineering and Biotechnology (IGB) will provide next generation sequencing (NGS) devices and perform NGS-based microbiological diagnostics. Moreover, IGB will calculate the individual SIQ scores in plasma samples of included newborns, infants, and toddlers with severe sepsis or septic shock.

### Eligibility criteria

5.2

Newborns (d0–d28), infants (d29 to <1 yr) and toddlers (1 yr to <5 yrs) with severe sepsis or septic shock (according to the pediatric sepsis definition) within the first 24 hours following onset (=time of diagnosis) are eligible for study inclusion. Further inclusion and exclusion criteria are described in detail in Tables 1 and 2.

**Table 1 T1:** Inclusion and exclusion criteria of the Next GeneSiPS-Trial.

Inclusion criteria septic patients	
Age <5 years	
Written declaration of informed consent from a parent/legal guardian.	
Proven or suspected severe Sepsis (with an onset ≤24 h)SIRS (Table 3) in the presence of or as a result of suspected or proven infection.AndAcute respiratory distress syndromeOrTwo or more other organ dysfunctions as defined in Table 2.	
Or Septic shock (with an onset ≤24 h)Sepsis and cardiovascular organ dysfunction as defined in Table 2.	
Inclusion criteria control patients	
Age <5 years	
Written declaration of informed consent from a parent/legal guardian.	
Children undergoing elective surgery under general anesthesia.	
Installation of a vein access and an indwelling urine catheter required as part of the elective operation.	
Exclusion criteria	
Age ≥5 years	
Refusal to give consent	
Patient will probably be discharged from the ICU within the first 72 h following inclusion	
Palliative treatment intent	
Clinician is not committed to aggressive treatment	
Death is deemed imminent and inevitable	
Patients who had previously been included, but are readmitted to the ICU during the same hospitalization, will not be included a second time.	

**Table 2 T2:** Organ dysfunction criteria as stated in the pediatric sepsis definitions^[23]^.

Organ system	Symptoms
Cardiovascular dysfunction	Despite the administration of isotonic intravenous fluid bolus ≥40 mL/kg in 1 h:• Decrease in BP (hypotension) <5th percentile for age or systolic BP <2 SD below normal for age^∗^OR• Need for vasoactive drug to maintain BP in normal range (dopamine >5 μg/kg/min or dobutamine, epinephrine, or norepinephrine at any dose)And• Two of the following- Unexplained metabolic acidosis: base deficit >5.0 mEq/L- Increased arterial lactate >2 times upper limit of normal- Oliguria: urine output >0.5 mL/kg/h- Prolonged capillary refill: >5 s- Core to peripheral temperature gap >3 °C
Respiratory^†^	• PaO_2_/FIO_2_ <300 mm Hg in the absence of cyanotic heart disease or preexisting lung diseaseOr• PaCO_2_ >65 torr. or 20 mm Hg over baseline PaCO_2_Or• Proven need^‡^ or >50% FIO_2_ to maintain saturation >92%Or• Need for non-elective invasive or noninvasive mechanical ventilation^§^
Neurologic	• Glasgow Coma Score ≤11^[65]^Or• Acute change in mental status with a decrease in Glasgow Coma Score ≥3 points from abnormal baseline
Hematologic	• Platelet count <80,000/mm3 or a decline of 50% in platelet count from highest value recorded over the past 3 days (for chronic hematology/oncology patients)Or• International normalized ratio >2
Renal	• Serum creatinine ≥2 times upper limit of normal for ageOr• 2-fold increase in baseline creatinine
Hepatic	• Total bilirubin ≥4 mg/dL (not applicable for newborn)Or• ALT 2 times upper limit of normal for age

Of note, pediatric and neonatal sepsis are defined slightly differently than sepsis in adults.^[23]^ While sepsis is defined in adults by the “Third International Consensus Definitions for Sepsis and Septic Shock (SEPSIS-3)” as “life threatening organ dysfunction caused by a dysregulated host response to infection”,^[1]^ the definition of pediatric sepsis is an adaptation of the previous version (SEPSIS-2),^[25]^ defining sepsis as the combination of ≥2 out of 4 criteria of a systemic inflammatory response syndrome (SIRS) (Table 3) due to an (probable) infection. “Severe sepsis” was characterized by an organ dysfunction in the context of sepsis, and “septic shock” was characterized by hypotension or the need of vasopressors despite adequate initial fluid resuscitation as a result of sepsis.^[25]^ The pediatric sepsis definitions, published 2005 by Goldstein et al,^[23]^ essentially adapt the included vital signs and laboratory variables taking into account the age-specific variations (Table 3). Comparable to SEPSIS-2, in the pediatric definition of sepsis, the term “severe sepsis” describes the combination of sepsis and organ dysfunction, which correlates closely with the definition of “sepsis” according to the “adult” SEPSIS-3 definition (Table 4). Therefore, it is not surprising that the international guidelines for the treatment of sepsis and septic shock in adults and children are very similar.^[8,11]^

**Table 3 T3:** Age-specific SIRS criteria.

Age group	Hart rate, L/min	Respiratory rate, L/min	Leukocyte count, L/nL	Systolic blood pressure, mm Hg	Temperature, °C
0d to 1 wk	<100 or >180	>50	>34	<65	<36 or >38.5
1 wk to 1 mo	<100 or >180	>40	>19.5 or <5	<75	<36 or >38.5
1 mo to 1 yr	<100 or >180	>34	>17.5 or <5	<100	<36 or >38.5
2–5 yrs	>140	>22	>15.5 or <6	<94	
6–12 yrs	>130	>18	>13.5 or <4.5	<105	
13–18 yrs	>110	>14	>11.0 or <4.5	<117	
SIRS criteria in adults	>90	>20	>12.0 or <4.0	NA	<36 or >38.0

**Table 4 T4:** Overview of sepsis definitions in children and adults.

	SEPSIS-1	SEPSIS-2	SEPSIS-3	Pediatric sepsis definition
Patient group	Adults	Adults	Adults	Pediatric
Authors	Bone et al^[68]^	Levy et al^[25]^	Singer et al^[1]^	Goldstein et al^[23]^
Year of publication	1992	2003	2016	2005
Sepsis	2/4 SIRS criteria	2/4 SIRS criteria or other sepsis symptoms out of a list		SIRS criteria age-adapted
Severe sepsis	Sepsis + organ dysfunction	Sepsis + organ dysfunction	Increase in SOFA-Score ≥2 points	Sepsis + organ dysfunction
Septic shock	Sepsis + hypotonia		Sepsis + hypotonia^∗^ + serum lactate ≥2 mmol/L	Sepsis + hypotonia

In addition, a total of 60 healthy children (20 neonates [d0–d28], 20 infants [d29 to <1 yr], and 20 toddlers [1 yr to <6 yr]) will be included in the study as reference to validate a pediatric SIQ-Score (pSIQ-Score).

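### Table 2 prints the oliguria criterion with an inequality that contradicts its label, and two further ambiguities in Tables 2 and 3 leave eligibility open to site interpretation

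*Protocol article*

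**What the plan says.** All of the text at issue is in section 5.2 (Eligibility criteria) of the protocol article.

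- **Table 1, septic shock route:** "Sepsis and cardiovascular organ dysfunction as defined in Table 2", with onset within 24 hours. Table 2 is therefore the operative rule.
- **Table 1, severe sepsis route:** "SIRS (Table 3) in the presence of or as a result of suspected or proven infection", together with ARDS or at least two other organ dysfunctions. Table 3 is therefore operative too.
- **Table 2, cardiovascular block:** after a fluid bolus, either hypotension, "Decrease in BP (hypotension) <5th percentile for age or systolic BP <2 SD below normal for age", or need for a vasoactive drug. The second limb runs straight into the list of five signs: "norepinephrine at any dose)And• Two of the following".
- **Table 2, third of the five signs:** "Oliguria: urine output >0.5 mL/kg/h".
- **Table 3, age rows:** birth to 1 week, 1 week to 1 month, 1 month to 1 year, then 2 to 5 years and older bands. The toddler stratum runs from 1 year to under 5 years.

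The Correction at the end of the article concerns Equation 3 only and leaves these tables as they stand.

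**The concern.** Oliguria is low urine output. The printed criterion is met by output above the cut-off, so the sign contradicts its own name, and no outside source is needed to see it. Because Table 1 refers to Table 2 for the definition, the contradiction sits in the inclusion rule and not in background text.

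The other two points are ambiguities. In Table 2, an OR followed by an And without brackets or indentation can be grouped in two ways. In Table 3, a child between the first and second birthday falls between two row labels whose limits differ widely.

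The stake is consistency across the 6 to 10 planned centres (section 5.12). A site that applies the tables as printed will classify some children differently from a site that silently corrects or interprets them. The shock classification and the case mix would then depend partly on who read the table.

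**Working it through.** The plan gives no figure to reproduce. The check sets out what the printed rules do to a given child.

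**1. The oliguria sign.** Let *m* be the number of the other four signs present (0 to 4). Two of five signs are required.

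| Child | Count as printed | Count if the label governs | Met as printed | Met if the label governs |
|---|---|---|---|---|
| Preserved output | *m* + 1 | *m* | *m* ≥ 1 | *m* ≥ 2 |
| Oliguric | *m* | *m* + 1 | *m* ≥ 2 | *m* ≥ 1 |

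The two versions disagree exactly when *m* = 1, and in opposite directions for the two kinds of child. With *m* = 0 neither version is met; with *m* ≥ 2 both are.

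A text-extraction fault is an unlikely cause: other < and > signs in the same table cell have come through.

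**2. The OR/And grouping.** Write A for hypotension, B for vasoactive need and C for at least two of five signs. A (yes/no), B (yes/no) and the sign count (0 to 5) give 2 × 2 × 6 = 24 combinations. C holds for 4 of the 6 counts (2, 3, 4, 5).

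- (A or B) and C: 3 combinations of A and B × 4 counts = 12 of 24 qualify.
- A or (B and C): A present, 2 × 6 = 12; A absent with B present, 1 × 4 = 4; total 16 of 24.
- Difference: 16 − 12 = 4 combinations, all with hypotension and zero or one sign, with or without a vasoactive drug.

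These are counts of logical combinations, not proportions of patients. Under the second grouping the oliguria sign matters only for a child on vasoactive drugs without hypotension. Under the first it matters for every child assessed by the cardiovascular criterion.

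**3. The age rows.** Taken at face value the labels leave months 12 to 23 without a row. That is 12 of the 48 months of the toddler stratum, or 25%. The age distribution within the stratum is not given, so this is not a share of children.

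Take an 18-month-old with heart rate 150 and respiratory rate 30:

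| Row used | Heart rate limits | Respiratory rate limit | Criteria met of these two |
|---|---|---|---|
| 1 month to 1 year | <100 or >180 | >34 | 0 |
| 2 to 5 years | >140 | >22 | 2 |

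The text of section 5.2 asks for at least two of four SIRS criteria, so the choice of row alone can decide whether SIRS is met. The blank temperature cells in the older rows may be merged cells broken in extraction and are not counted here.

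**The case against.** The strongest defence is about consequence. The study is observational and exploratory, its p-values are described as descriptive (section 5.16), and NGS and culture are compared case by case, so a slip in inclusion does not bias the comparison within a child. Children can also enter through ARDS or two other organ dysfunctions. Eligibility is tied to a published pediatric definition that all sites can consult, and clinicians may well follow the word oliguria rather than the sign. Table 2's footnotes are not in the text at hand. All of this limits the damage. None of it removes the contradiction from the operative table.

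On the age rows, the later bands (2–5, 6–12, 13–18) join up only if they mean completed years. On that convention the row ending at 1 year could extend to the second birthday. Against this, the first three rows share their endpoints, and the trial's own infant group ends before 1 year. Both readings are tenable, so this is an unclear label and not a contradiction.

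A reader might infer more than the documents support:

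- **That the text sets a rival shock rule.** The text says septic shock "was characterized by hypotension or the need of vasopressors despite adequate initial fluid resuscitation as a result of sepsis", without further signs. That sentence describes and cites SEPSIS-2, the adult definition; the pediatric one is introduced separately afterwards. Table 4 gives "Sepsis + hypotonia" for children, but it is an overview, and it conflicts with Table 2 only under the grouping (A or B) and C.
- **That the share of misclassified children can be calculated.** This would need one of the two groupings, invented prevalences for the signs, and independence between signs of the same dysfunction.
- **That systolic pressure is a fifth SIRS criterion.** Table 3 has such a column, but its adult row shows it as not applicable, and the text speaks of four criteria. Only the table title is loose.
- **That enrolled children need re-screening.** Section 6.2 places the start of recruitment in the future, and no enrolled child is documented.

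**Conclusion.** The oliguria criterion is wrong as written: its inequality contradicts its label, inside the table that defines septic shock for inclusion. Where the two-sign requirement applies, the result reverses for any child with exactly one of the other four signs.

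The OR/And grouping and the row for 12 to <24 months are lesser problems of clarity. Each can still change whether a given child meets a criterion: hypotension with fewer than two signs in the first case, zero or two SIRS criteria for the example child in the second.

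The net effect on enrolment is unknown. The documents give neither the frequency of the signs nor the ages within the toddler stratum, and the other organ-dysfunction route may admit some of the same children. The conclusion rests only on the printed wording of Tables 1 to 3 and on oliguria meaning low output.

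**What to change.** Before enrolment:

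1. Reconcile the oliguria inequality in Table 2 with its label and with the pediatric definition that the protocol cites.
2. State the grouping of OR and And in the cardiovascular block, so that it is clear whether the two further signs apply to hypotension as well as to vasoactive need.
3. State which row of Table 3 covers 12 to <24 months.
4. Apply the same logic at all sites. The eCRF is not shown, so whether it already contains an eligibility check cannot be judged; if it does, it should match the reconciled tables.

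No threshold or clinical rule is proposed here; those decisions are the sponsor's. The cost is a text correction, with the written approval and ethics assessment that section 5.22 requires for protocol changes, and at most an adjustment to the eligibility check. No additional patients are needed.

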### Sample size

5.11

For reasons of feasibility, only 150 children (50 neonates [≤28 d], 50 infants [29 d to <1 year], and 50 children up to preschool age [1 year up to the age of <5 years]) will be included in this study. Due to the exploratory nature of this trial no concrete sample size calculation has been performed. However, the Next GeneSiPS-Trial is to be seen in the context of the Next GeneSiS-Trial,^[22]^ in which a total of 500 adult patients with sepsis/septic shock are included.

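### Table 2 labels a sign of cardiovascular dysfunction as oliguria but prints the urine-output inequality in the opposite direction, in a criterion that decides septic-shock entry

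*Protocol article*

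**What the plan says.** Section 5.2 of the protocol article refers the reader to Tables 1 and 2 for the detailed entry criteria. Table 1 admits a child with septic shock of recent onset on the basis of "Sepsis and cardiovascular organ dysfunction as defined in Table 2". The other septic route in Table 1, severe sepsis, requires acute respiratory distress syndrome or at least two other organ dysfunctions from Table 2.

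Table 2 is captioned "Organ dysfunction criteria as stated in the pediatric sepsis definitions". Its cardiovascular row starts from a state that persists despite a fluid bolus. It gives a blood-pressure criterion, then OR, then need for a vasoactive drug, then And, then "Two of the following". Five signs follow: metabolic acidosis, raised lactate, oliguria, prolonged capillary refill and a core-to-peripheral temperature gap. The third is printed as "Oliguria: urine output >0.5 mL/kg/h".

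No other part of the article gives a urine-output criterion. The published Correction at the end concerns Equation 3 only.

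**The concern.** The word and the symbol on the same line cannot both be applied. Oliguria is low output, while the printed test is met by output above the cut-off and failed by output at or below it. The line belongs to an entry criterion, so it bears on who is enrolled.

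The error acts in both directions. A child with preserved output is credited with a sign that the label does not give. A child with low output is denied a sign that the label does give. Section 5.12 plans 6 to 10 centres with 50 children per age group. If one site works from the word and another from the symbol, for instance because the symbol was copied into an eCRF eligibility form, their septic-shock patients could differ in severity. Severity may in turn bear on culture positivity and on how many children fall into the treatment-failure subgroup of sections 5.4 and 5.16.

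**Working it through.** **No plan figure to reproduce.** The article states that "no concrete sample size calculation has been performed", and this point does not depend on power or alpha. The check covers the label, the inequality and the counting rule.

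**Is it a text-extraction fault?** Unlikely. In the same table cell the less-than sign survives in "Decrease in BP (hypotension) <5th percentile for age". The other four supporting signs all use a greater-than sign in the direction of abnormality, so a symbol carried down the list is a plausible explanation.

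**Who is affected?** Let K be the number of the other four signs that are present. The two-sign rule needs K plus the urine sign to be at least 2.

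- K = 0: not met under either direction.
- K of 2 or more: met under either direction.
- K = 1: the urine sign decides. As printed, the rule is met if output is above the cut-off. By the label, it is met if output is low.

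Only children with exactly one other sign change status. Those with output above the cut-off gain entry, and those with low output lose it.

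**Pattern count, without assumptions on frequency.** The other four signs have 2^4 = 16 patterns, of which 1 has K = 0, 4 have K = 1 and 11 have K of 2 or more.

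| Urine output | Patterns meeting the rule, as printed | Patterns meeting the rule, by the label |
|---|---|---|
| Above the cut-off | 15 of 16 | 11 of 16 |
| Low | 11 of 16 | 15 of 16 |

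These are patterns, not proportions of patients.

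**Illustration of the net effect.** Assumption (no document gives these frequencies): among children to whom the rule applies, the five signs are independent and each is truly present in a share q.

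- By the label: P = 1 − (1−q)^5 − 5q(1−q)^4.
- As printed, the urine sign has probability 1−q: P = (1−q)·[1 − (1−q)^4] + q·[1 − (1−q)^4 − 4q(1−q)^3].
- Difference, printed minus label: (1−2q)·4q(1−q)^3. For q between 0 and 1 the sign depends only on whether q is below or above one half.

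| q | By the label | As printed | Difference |
|---|---|---|---|
| 0.20 | 0.263 | 0.508 | +0.246 |
| 0.30 | 0.472 | 0.636 | +0.165 |
| 0.40 | 0.663 | 0.732 | +0.069 |
| 0.50 | 0.8125 | 0.8125 | 0 |
| 0.60 | 0.913 | 0.882 | −0.031 |

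Worked check at q = 0.60. By the label: 1 − 0.01024 − 0.0768 = 0.913. As printed: 0.4 × 0.9744 + 0.6 × 0.8208 = 0.38976 + 0.49248 = 0.882.

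Under independence, then, literal use loosens the rule if each sign is present in under half of the children, leaves it unchanged at half, and tightens it above half.

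**How far the rule reaches.** The OR/And layout can be read in two ways. If the two-sign rule qualifies both the blood-pressure and the vasoactive-drug branches, the table above applies to all children in either branch. If it qualifies only the vasoactive-drug branch, hypotension after the fluid bolus is enough by itself and the urine line affects fewer children. Table 4, which summarises pediatric septic shock as sepsis with low blood pressure, does not settle this.

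**The case against.** The strongest reply is that the intent is plain. The line is headed oliguria, it stands among signs of poor perfusion, the table claims to follow a cited definition, and the readers are pediatric and neonatal intensive care physicians. The full protocol and the eCRF are not shown and may already be right. All of this stands. It lowers the chance that sites were misled, but it does not remove a contradiction from a published entry criterion.

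The reply also limits the reach. The urine sign alone never establishes cardiovascular dysfunction. A child who loses it may qualify on the other four signs, or enter as severe sepsis through acute respiratory distress syndrome or two other organ dysfunctions. That also stands.

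Four stronger readings are tempting and are not supported:

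- *Entry is clearly loosened.* This holds only if each sign is present in under half of the children concerned. These children are already hypotensive or on vasoactive drugs despite fluid, so a share of one half or more is plausible, and there the effect vanishes or reverses.
- *Septic shock is compromised as a stratum.* The article declares no such stratum. Groups are by age (section 5.11), and the planned subgroup is treatment failure (sections 5.4 and 5.16).
- *The error could not be undone afterwards.* Section 5.8 lists fluid balance and not urine output, but that is a condensed list, and section 5.17 allows monitors to check entries against source documents.
- *Sites will enrol different children.* No passage shows this. It is a possibility.

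**Conclusion.** The contradiction is certain and rests on the article alone: in one of five supporting signs, the label and the inequality point in opposite directions, and Table 1 makes the definition operative for septic-shock entry.

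The size and direction of its effect on enrolment are unknown. They depend on how common the signs are and how they cluster, on whether the two-sign rule covers one branch or both, on entry by other routes, and on how many sites follow the symbol. The range of +25 to −3 percentage points for q from 0.20 to 0.60 is an illustration under independence and equal frequency, not an estimate.

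The main comparison is unaffected in kind. Section 5.16 compares sequencing with culture case by case in the same child, using McNemar's test and kappa, and treats P-values as descriptive. A shift in case mix could change the value of kappa or the population to which the results apply, but it does not break the pairing. This is a correction worth making at almost no cost, and not a flaw that threatens the study's validity.

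**What to change.** 1. Reconcile the label and the inequality in Table 2 with the cited pediatric sepsis definition, and carry the same wording into the eCRF eligibility form and the site instructions. At the same time, state whether the two-sign rule applies to both the blood-pressure and the vasoactive-drug branches.
2. Record in the eCRF the urine output that was used for eligibility.
3. Re-check against source documents any child whose septic-shock entry relied on the printed sign.

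The cost is an edit to one table row, one eCRF field, and a source check limited to children for whom this sign was decisive. It requires no change to the sample size or the analysis.
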